## Abstract

**Background:**

Mindfulness-based intervention (MBI), an emotion-focused approach, has been shown promising and sustainable effects on enhancing the well-being of caregivers of patients with dementia (PWD). However, the conventional MBI was quite demanding, had high rates of attrition and inconsistent long-term effect. The social distancing measures introduced during the COVID-19 pandemic also restricted face-to-face psychosocial intervention. The study aims to evaluate the effectiveness of a 6-week hybrid MBI in caregivers of PWD over a 6-month follow up.

**Methods:**

This is a single-blinded, parallel-group randomized controlled trial (RCT). Eligible participants from three local nongovernmental organizations (NGOs) will be randomly divided into intervention groups and control groups in a ratio of 1:1. The participants in the intervention group will receive 6 weekly 90-min group-based sessions delivered through a face-to-face and online approach. The participants in the control group will receive brief education on dementia care with the same group size, duration, and frequency as the sessions in the intervention group. Immediately after the intervention and at the 6-month follow-up, caring stress and other outcomes will be assessed. Besides, a focus group interview will be conducted to identify the strengths, limitations, and therapeutic components of the intervention from their perspectives. For quantitative data, intention-to-treat analysis and Generalized Estimating Equations (GEE) will be used. For qualitative data, content analysis will be used.

**Discussion:**

This proposed hybrid model of MBI has several advantages, such as lower duration, longer follow-up period and easier access by family caregivers. Also, physiological indicators (e.g., heart rate viability and neuropsychiatric symptoms) will be measured in this study to show the body change after MBI. The quantitative and qualitative data of this research can also benefit the development of online or hybrid MBI for caregivers of PWD during the COVID-19 pandemic. Despite these strengths, it does have practical challenges and limitations. However, this proposed intervention has the potential to benefit not only the participants, but also the researcher as well as public health providers.

*Trial registration*: NCT05242614. Registered on 2022-02-16, https://clinicaltrials.gov/ct2/show/NCT05242614

## Background

Dementia is a worldwide public health priority that currently affects over 50 million people around the world, the number is expected to increase to 152 million by 2050 [1]. Similarly, the number of dementia cases in Hong Kong is predicted to triple from 100,000 cases in 2009 to 300,000 in 2039 [2]. Dementia is a syndrome that features a progressive and irreversible decline in cognitive functioning. It impairs one’s independent functioning and affects one’s daily living [3]. Over 90% of patients with dementia (PWD) experienced a range of behavioural and psychological symptoms of dementia (BPSD) including wandering, depression, and agitation [4]. Family caregivers of PWD involve in multiple caregiving tasks, such as aiding everyday activities of PWD and managing their BPSD. They also need to balance these caregiving tasks with other demands, such as their own career and social events [5, 6]. The caregiving burden, uncertainty about the progression of the disease, and family conflicts contributed to a high level of caregiving stress in caregivers [7]. Such stress can last for a decade, or until the care recipients passes away. The prolonged and high levels of stress could also put caregivers’ physical health at risk, resulting in various problems such as insomnia, high blood pressure, poorer immune function, a higher risk of developing other psychological symptoms and cardiovascular events [8–10]. Consequently, the high level of stress and poor psychological health of the caregivers will further affect the dyadic relationship, which may worsen the BPSD of the PWD [11]. Reducing the stress experienced by family caregivers can improve their physical and psychological well-being, dyadic relationship, and build their resiliency to take care of their PWD for a longer period of time. Moreover, the social distancing restriction during COVID-19 led to the suspension and reduction of community-based, as well as home care services for PWD. PWD felt frustrated and expressed anger to caregivers for staying at home [12]. The mental well-being of the caregivers was significantly affected due to isolation and limited respite. A research reported that the pandemic further increased the caregiver of PWD’s stress and anxiety level, particularly for those caring for patients with severe dementia [13]. Thus, stress reduction for caregivers is not only recommended but an imperative, especially during the time of Covid-19 [14].

### Rationale for using mindfulness and the conceptual framework

In the recent decade, there has been growing attention to mindfulness due to its effectiveness in stress reduction. Mindfulness features the practice of awareness, attention, and remembering [15]. It includes different types of practices such as sitting mediation, mindful eating, body scanning and mindful walking. It is effective in improving psychological symptoms, including anxiety, depression, psychotic symptoms, and stress in various populations [16]. A recent meta-analysis of 131 randomized controlled trials found that mindfulness training has promising and sustainable effects on enhancing the well-being of caregivers of PWD, compared with other psychosocial interventions, such as counselling and support groups [17]. The potential mechanism of mindfulness in stress reduction can be explained by the mindful coping model (Fig. 1) [18]. As illustrated in the figure, mindfulness training can assist participants to step outside their negative experience and de-centre their sources of stress, and hence allowing caregivers to broaden their attention. Such a shift of attentional focus thereby allowed caregivers to generate a new meaning of the caregiving situations in the process of stress reduction and positive appraisal [19]. By objectively observing from a distance by stepping outside of the mind, participants will be able to realize that their mental events are not unchangeable truths, but only a constructed reality of the self [16].

**Fig. 1 Fig1:**
[figure not shown]
Mindful coping model (adopted from Garland et al. [18]; permission obtained from Elsevier License Number: 5301780254130)

Moreover, mindfulness and mediation are also useful for improving mental health during the COVID-19 pandemic. A research revealed that mindfulness practitioners, compared to non-mindfulness practitioners, reported having a lower level of depression, anxiety and pandemic-related distress [20]. Therefore, mindfulness training can be beneficial for caregivers to reduce stress during the pandemic.

### Existing challenges of applying the original MBI on family caregivers of PWD

Despite the usefulness of mindfulness, the feasibility of using the original MBI program on family caregivers of PWD is in doubt due to the intensiveness of the program. The original MBI protocol requires participants to commit over 27 h of practice within 8-weeks time. The program's intensiveness could potentially discourage family caregivers from participating, as they spent on average 21–63 h a week in taking care of the PWD [7].

A systematic review on the MBI program for family caregivers of PWD identified five MBI trials in the field [21]. Of these studies, most adopted the original MBI intervention (150-min weekly session for 8 weeks, together with 45 min of mindfulness practice per week and a 7.5-h retreat). Although this review suggested that the original MBI program had an immediate moderate effect in stress reduction on family caregivers, a high attrition rate was found ranging from 10.5 to 17.2%. Other mindfulness studies targeting family caregivers of PWD suggested similar challenges. Family caregivers shared their difficulty in attending the sessions and practicing mindfulness at home due to their busy caregiving schedule. Some also reflected that the contents should be relevant to dementia caregiving so that they can apply mindfulness skills in their daily caregiving tasks (e.g., responding mindfully to the PWD) [22]. The social distancing measures introduced during COVID-19 also created challenges for conducting face to face MBI program. The original MBI program involved group activities that may increase the risk of infection. All these findings and the social restriction during COVID-19 seem to suggest that there is an need to modify the original MBI program to better suit the needs of family caregivers of PWD and minimize the chance of social contact.

### The rationale for using a simplified version of mindfulness programme

Developing a more simplified and less intensive mindfulness program could be a viable solution. A recent review of the duration of mindfulness training showed there was no association between the number of in-class hours spent on mindfulness training and the psychological outcomes of various participants. This implied that a MBI program with a longer duration would not yield a more significant effect on the psychological outcomes of the participants after they had learnt and mastered the skills of mindfulness [23], suggesting that a original MBI program with a total of 27 training hours may not be necessary. A three-arm study conducted by Demarzo et al. also found that those who participated in either an eight or four sessions MBI demonstrated significant improvements in different psychological outcomes compared to the control (usual care) group at the 2 and 6 month follow-ups, with similar effect size (0.42 vs 0.45 in depression, 0.15 vs 0.13 in resilience, 0.46 vs 0.57 in anxiety) at the 6-month follow-up [24].

There are existing studies which adopted a less intensive MBI, and these studies seem to suggest a more positive finding regarding its feasibility and effectiveness for family caregivers of PWD. A 7-session group-based MBI program for family caregivers of PWD (total 14 h trainings) was carried out and evaluated in a RCT design [25]. Compared to the educational control group, the MBI group significantly reduced stress, depressive symptoms, and BPSD-related caregivers’ distress immediately after the program and 6-month after. The completion rate was over 83% and the attrition rate was only at 11.1%. Most caregivers could practice mindfulness 180 min per week. From the interviews of the same study, caregivers suggested a less intensive approach and a more flexible delivery mode can potentially lead to more widespread use of mindfulness in dementia caregiving.

In addition, the original MBI programme requires the involvement of a qualified interventionist who has undergone rigorous training in mindfulness and completed all of the modules (1 to 4) in a course for teachers of mindfulness or a person who has obtained a master’s degree from the Oxford Mindfulness Centre, which usually takes 2–3 years. This may impede the popularization of practising mindfulness for family caregivers of PWD. We agree that it is essential for an interventionist to receive rigorous training in order to deliver the MBI for a clinical population with some severe psychological problems (e.g., patients with severe depression). However, we suggested that a simplified version of an MBI protocol with a smaller number of sessions is needed for non-clinical caregivers of PWD to promote mindfulness practice.

### The rationale for using a hybrid programme of face-to-face and online delivery

The adoption of a more flexible delivery mode of the MBI intervention could make the program even more tailored to the needs of family caregivers. In recent years, the use of online MBI has gained much attention in the field [26]. However, a meta-analysis suggested that compared to face-to-face MBIs, the purely digitalized MBIs only had a limited effect in reducing family caregiver’s depression and anxiety symptoms (with an effect size of less than 0.4) [19]. The lower efficacy of the purely digital MBI can potentially be explained by the absence of in-person guidance given by the mindfulness therapist at classes. In face-to-face MBI, the mindfulness teacher/facilitator not only teaches mindfulness skills but also helps caregivers to learn and practise mindfulness in person [19]. Receiving mindfulness training through a purely online learning approach may not provide sufficient guidance to caregivers, and hence, caregivers may not learn and master mindfulness skills well.

Using a hybrid approach to deliver the MBI is a possible solution to this problem [27]. A meta-analysis of online education revealed that learning was more effective in hybrid and blended programs than face-to-face or purely online programs [28]. A hybrid MBI program contains both face-to-face and online features which can complement the strengths and weaknesses of face-to-face MBI sessions and online sessions. An online platform containing different self-directed learning materials makes it easier for caregivers to receive the training without interruption. Conversely, face-to-face sessions can provide caregivers opportunities to develop peer support through sharing their experiences and difficulties in practicing mindfulness with peers and the mindfulness facilitator. Moreover, the hybrid MBI program also minimizes the chance of group gathering and the risk of COVID-19 infection. It also provides flexibility for caregivers to attend the program as they need additional time for caregiving PWD at home during the pandemic.

In view of the limitations of previous studies, we will advance the intervention protocol and further investigate the scope of using mindfulness in dementia caregiving in this study. To overcome the challenges of time constraints imposed by the caregiving tasks and social distancing measures during the COVID-19 pandemic, we will adopt a simplified mindfulness protocol which includes only three face-to-face sessions and self-directed learning materials through hybrid mode. Furthermore, we have integrated several new components about dementia caregiving in the protocol such as mindful communication with people with dementia and exercises focusing on unpleasant caregiving experiences to strengthen the application of mindfulness in caregiving tasks. Based on the qualitative findings from our previous studies [25], we will also investigate the intervention effects on various caregiving outcomes such as dyadic relationship and positive aspect of caregiving that were rarely investigated in previous mindfulness studies. To the best of our knowledge, this is the first study investigating the effects of a simplified version of mindfulness programme for the family caregivers of PWD via hybrid mode.

## Methods

### Objectives

The objectives of the protocol are: (1) to examine the effects of a 6-week, hybrid (face-to-face and online) mode of a MBDCP on perceived caregiving stress of caregivers of PWD immediately after 6-week intervention and over a 6-month follow-up period; and (2) to identify the strengths, weaknesses and therapeutic components of the program from the views of family caregivers.

### Design

This protocol’s flow follows the CONSORT Diagram (Fig. 2) (http://www.consort-statement.org/)_and SPIRIT Flow Diagram (Fig. 3) (https://www.spirit-statement.org/).

**Fig. 2 Fig2:**
[figure not shown]
Consort Flow diagram of the study

**Fig. 3 Fig3:**
[figure not shown]
SPIRIT Flow diagram of the study

This study adopts a mixed-method design to achieve the study objectives. A single-blinded, parallel-group randomized controlled trial (RCT) is used to evaluate the effect of the intervention (Fig. 2). Focus group interviews will be conducted to explore the participants’ experience attending the program and the short-term and long-term impacts on caregiving.

### Subjects and settings

In this study, family caregivers of PWD will be recruited from three local nongovernmental organizations (NGOs) that provide dementia care services (e.g., cognitive training, respite care) in Hong Kong. A family caregiver is defined as an unpaid individual who has a significant relationship with the PWD and is involved in providing assistance with daily life.

The participants will be eligible if they are family caregivers: (1) aged ≥ 18; (2) taking care of a family member who is diagnosed with dementia who has been residing in the community; and (c) providing care for at least 6 months prior to the subject recruitment. Caregivers will be excluded if (1) they have participated in any structured psychosocial intervention or mindfulness-based intervention/training in the 6 months prior to recruitment, (2) have acute psychiatric and medical comorbidities that are potentially life-threatening (e.g., suicidal ideation) or leave them with a limited ability to participate or adhere to the intervention (e.g., acute psychosis), or (3) do not have Internet access.

For the qualitative arm, purposive sampling will be adopted to select equal proportions of caregivers with different level of improvement in their stress (measured via Perceived Stress Scale) to join the focus groups.

### Sample size

The sample size is estimated based on the primary outcome of our study (perceived stress). This proposed study will adopt a simplified version of mindfulness training that differs from the protocol in our prior RCT [25]. Therefore, after considering the effect size of 0.36 in the prior meta-analysis on cognitive behavioural interventions for reducing stress in family caregivers of PWD [29], we adopted a conservative medium effect size of 0.40, which is similar to the effect size of psychological and behavioural interventions suggested by Cohen, to detect the mean difference in stress reduction between the intervention and control groups [30]. Considering the 20% attrition rate at 6 months that we found in our prior study, a sample size of 290 family caregivers (145 per group) is needed to achieve 80% power at 5% significance level (Two-sided). 20 caregivers from the intervention group will be purposively sampled to join in a focus group with a group size of 4 to 5 dyads per group one week after the intervention. After the intervention, equal proportions of participants with different levels (e.g., high, moderate, and low) of stress reduction will be selected.

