The reduction of in-person support services during the outbreak of COVID-19 started a digital revolution for dementia care [49]. Digital technologies, such as video conferencing platform, has become widely adopted in psychosocial intervention for caregivers of PWD. The effectiveness of internet-based and web-based mindfulness intervention for caregivers of PWD is well documented [50]. This study can further provide evidence on the feasibility and effectiveness of a hybrid psychosocial intervention for caregivers of PWD during the COVID-19 pandemic. The result of the MDBCP will also be useful and crucial for future development on online and hybrid care support for caregivers of PWD.

Despite the above advantages, we foresee there are practical challenges when conducting this study. First, a large samples size of 290 participants is required. Subject recruitment could be particularly difficult under the COVID-19 pandemic. But we believe the online component of our program, compared to the original face to face MBI, could attract more family caregivers to take part in the study. To maximize the recruitment, the recruitment strategy of this study should focus on the unique strength of the program in which the hybrid component can give caregivers more flexibility to take part in the study according to their schedule. Second, it is common for participants to have a relatively low motivation for online learning compared to face-to-face sessions due to the absence of an actual interventionist on site. Participants may skip some online materials or forget to attend some sessions. To minimize the impact of this, we designed some follow-up sessions between each online session to prompt participants to complete the sessions. Third, in this study, only the researcher is blinded to the group allocation, and hence, there is a chance of bias as participants are aware of their group allocation. But we attempted to minimize such bias by measuring the level of mindfulness of participants so that we can examine whether the intervention effect we observed is contributed by the enhancement of mindfulness.

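### The stated 290 does not follow from the printed sample-size inputs, which give 250, and the effect size of 0.40 is called conservative although it exceeds the 0.36 cited beside it

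*Protocol article*

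**What the plan says.** The Sample size section bases the trial on perceived stress and aims "to detect the mean difference in stress reduction between the intervention and control groups". It chose the effect "after considering the effect size of 0.36 in the prior meta-analysis on cognitive behavioural interventions for reducing stress in family caregivers of PWD", and then states: "we adopted a conservative medium effect size of 0.40". It adds that this resembles a conventional benchmark for psychological and behavioural interventions. The attrition allowance is introduced with "Considering the 20% attrition rate at 6 months that we found in our prior study", and the conclusion is that "a sample size of 290 family caregivers (145 per group) is needed to achieve 80% power at 5% significance level (Two-sided"). The Abstract gives 1:1 allocation. The Discussion repeats that "a large samples size of 290 participants is required".

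The Sample size section names no design effect, multiplicity adjustment, baseline correlation or non-parametric correction.

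On attrition, the Background section on the simplified programme says of the seven-session trial that the Sample size section calls the team's prior RCT: "The completion rate was over 83% and the attrition rate was only at 11.1"%. It gives no time point for that figure.

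**The concern.** The section prints every input that a two-group comparison of means needs, and also the result, and the two disagree. This is not a detail left to an analysis plan. A reader who checks the figure cannot tell which assumption the trial rests on, and the claim of 80% power is not what 290 delivers at 0.40.

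The word conservative points the wrong way beside the evidence given. A larger assumed effect lowers the required sample size, so moving from 0.36 to 0.40 is the less cautious choice relative to that source. What is at stake is the accuracy of the planning statement for the primary outcome, and how the power claim will be read if the true effect is nearer 0.36.

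**Working it through.** **Inputs** (Sample size section, with allocation from the Abstract): standardised effect d = 0.40, two-sided alpha 0.05, power 80%, attrition 20%, 1:1 allocation. Stated result: 290, or 145 per arm.

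**Step 1. Attempt to reproduce 290.**
- Normal approximation: n per arm = 2(1.960 + 0.842)² / d² = 15.70 / 0.16 = 98.1, so 99.
- Two-sample t-test (noncentral t): 99.1, so 100 per arm.
- Attrition: 100 / 0.80 = 125 per arm, **250 in total**. From the normal approximation, 99 / 0.80 = 123.75, so 124 per arm and 248 in total.
- Excess of the stated figure: 290 − 250 = 40, and 40 / 250 = 16%.
- Multiplying by 1.2 instead of dividing by 0.8 gives 240 (238 by the normal approximation). A one-sided test gives 196. Neither explains 290.

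**Step 2. Unstated inputs that would give 290 or close to it.**

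| Unstated input | Calculation | Total |
|---|---|---|
| d = 0.37, 20% attrition | 116 / 0.80 = 145 per arm | 290 |
| d = 0.36, 15% attrition | 123 / 0.85 = 144.7, so 145 per arm | 290 |
| d = 0.40, 20% attrition, design effect 1.16 | 100 × 1.16 / 0.80 = 145 per arm | 290 |
| d = 0.40, 20% attrition, rank-test efficiency factor 0.864 | 100 / 0.864 / 0.80 = 144.7, so 145 per arm | 290 |
| d = 0.40, 20% attrition, 85% power | 114 / 0.80 = 142.5, so 143 per arm | 286 |

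For the group sizes of 15 to 18 in the Interventions section, a design effect of 1.16 corresponds to an ICC of 0.16 / (m − 1): 0.011 at m = 15 and 0.009 at m = 18. Nothing in the document favours any of these routes.

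**Step 3. What 290 delivers.** Retained per arm: 145 × 0.80 = 116. The noncentrality is d√(116/2), on 230 degrees of freedom.
- d = 0.40: 0.40 × 7.616 = 3.05, power **85.8%**.
- d = 0.36: 0.36 × 7.616 = 2.74, power **77.9%**.
- Effect detectable with 80% power: 0.369.

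**Step 4. What 0.36 would need.** 123 evaluable per arm; 123 / 0.80 = 153.75, so 154 per arm and 308 in total, 18 more than planned.

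Steps 3 and 4 treat caregivers as independent. Both arms are delivered in groups of the same size (Interventions and Control group sections), so any within-group correlation would lower these powers.

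**The case against.** **The error is on the safe side.** This stands. More caregivers are planned than the printed inputs require, and at 0.40 the power exceeds the claimed 80%. A reader might infer that the trial is underpowered. The document does not support that: its power claim is made for 0.40, not 0.36, and even at 0.36 the shortfall is about 2 percentage points before clustering.

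**0.40 may be conservative against something else.** The 0.36 comes from cognitive behavioural interventions and was only considered, and the section also appeals to a general benchmark. The Background reports a moderate immediate stress effect for the original mindfulness programme. The authors may mean conservative relative to that, but the Sample size section gives no larger stress effect, so the word remains unsupported as written.

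**The attrition figures need not conflict.** A reader might infer that 20% contradicts the 11.1% reported for the prior RCT. That is not established. The 20% sentence cites no study, the Interventions section refers to both a pilot and a main study, and the 11.1% carries no time point while the 20% is placed at six months. A different study or time point could account for both. Using 20% also raises the sample size, so it does not harm power.

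**An effect of 0.37 reproduces 290 exactly.** It is tempting to treat 0.37 as the value used, but Step 2 shows other routes that fit equally well.

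**Conclusion.** The arithmetic point holds. On the printed inputs the requirement is 250 (248 by the normal approximation), not 290, a gap of 16% that no stated factor explains. With 20% attrition and 290 recruited, power is about 86% at 0.40 and about 78% at 0.36, assuming a two-sample comparison of means with independent participants. Describing 0.40 as conservative is unsupported by the evidence given with it.

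This is a fault in the reported sample-size statement. It does not show that the trial is too small for its adopted effect. The attrition point is only a request for clarification.

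**What to change.** Keep 290 and rewrite the paragraph:

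- State the formula or software procedure, and the effect size or inflation factor that actually led to 145 per arm. The authors should supply this from their records; neither 0.37 nor a particular ICC should be adopted because it happens to fit.
- If no other factor was used, replace the 80% claim with about 86% power at 0.40 and about 78% at 0.36, noting that both are before any allowance for group clustering. If the excess was a clustering allowance, say so and give the design effect.
- Drop the word conservative, or justify it against a stated, larger stress effect with its source.
- As a minor point, give the source and time point of the 20% attrition, and the time point of the 11.1%.

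The cost is one paragraph of text, with no change in enrolment or analysis. If no other factor was used, the text will show power below 80% at the cited 0.36.
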